### 5.2 Exclusion Criteria

Patients are excluded from the study if any of the following criteria apply (or any of the criteria from the appropriate sub-protocol):

1. Patients who have previously had a score of 6 or 7 on the 9-point ordinal scale.
2. Any patient whose interests are not best served by study participation, as determined by a senior attending clinician.
3. Alanine aminotransferase (ALT)/aspartate aminotransferase (AST)  $> 5 \times$  the upper limit of normal (ULN).

4. Known active infection with HIV or hepatitis B or C.
5. Stage 4 severe chronic kidney disease or requiring dialysis (ie, estimated glomerular filtration rate  $<30$  mL/min/1.73 m^2).
6. History of the following cardiac conditions:
  - a) Myocardial infarction within 3 months prior to the first dose
  - b) Unstable angina
  - c) History of clinically significant dysrhythmias (long QT features on electrocardiogram [ECG], sustained bradycardia [ $\leq 55$  bpm]), left bundle branch block, cardiac pacemaker or ventricular arrhythmia) or history of familial long QT
7. Screening 12-lead ECG with a measurable QTc interval according to Fridericia correction (QTcF)  $>500$  ms.
8. Anticipated transfer to another hospital that is not a study centre within 72 hours.
9. Allergy to any study medication.
10. Experimental off-label usage of medicinal products as treatments for COVID-19.
11. Patients participating in another clinical study of an investigational medicinal product.
12. Active tuberculosis defined as requiring current treatment for tuberculosis.

### **5.3 Lifestyle Considerations**

Any lifestyle considerations that are specific to the candidate agent will be defined in the corresponding sub-protocol.

Female patients are advised to avoid becoming pregnant during the study.

### **5.4 Screen Failures**

Screen failures are defined as patients who consent to participate in the clinical study but are not subsequently randomly assigned to study treatment. A minimal set of screen failure information is required to ensure transparent reporting of screen failure patients to meet the Consolidated Standards of Reporting Trials (CONSORT) publishing requirements and to respond to queries from regulatory authorities. Minimal information includes demography, screen failure details, eligibility criteria, and any serious adverse event (SAE).

## **6.0 STUDY TREATMENT**

Study treatment is defined as any investigational treatment(s), marketed product(s), placebo, or medical device(s) intended to be administered to a patient according to the study protocol.

### **6.1 Study Treatment(s) Administered**

This platform study will include multiple treatments (candidate agents) from different pharmaceutical companies. Each candidate agent included within the study will have a sub-protocol that will provide details of that treatment, including route and mode of administration, dose, dosage regimen, and duration of treatment.

These candidate agents may include, but will not be limited to, anti-virals, human plasma-derived agents, or immunomodulatory agents; experimental (first-in-human) agents will not be considered as candidate agents.

The SoC will be based on appropriate guidelines in place at the time of treatment on the study, eg, the current National Institute for Health and Care Excellence ‘COVID-19 rapid guideline: critical care in adults’. The SoC may change during the course of the study as new information becomes available about treating COVID-19.

### **6.2 Preparation/Handling/Storage/Accountability**

Candidate agents will be shipped to the study centre either directly from participating companies, from the Sponsor, or from other regional or local drug repositories. All other supplies will be provided by the study centre.

The Investigator or designee must confirm appropriate temperature conditions have been maintained during transit for all candidate agents received and any discrepancies are reported and resolved before use of the candidate agent.

Only patients enrolled in the study may receive a candidate agent and only authorised study centre staff may supply or administer candidate agents. All candidate agents must be stored in a secure, environmentally controlled, and monitored (manual or automated) area in accordance with the labelled storage conditions with access limited to the Investigator and authorised study centre staff.

The Investigator, institution, or the head of the medical institution (where applicable) is responsible for candidate agent accountability, reconciliation, and record maintenance (ie, receipt, reconciliation, and final disposition records).

Further guidance and information for the final disposition of unused candidate agents are provided in the Pharmacy Manual for the candidate agent.

The Investigator, a member of the study centre staff, or a hospital pharmacist must maintain an adequate record of the receipt and distribution of all candidate agents using the Drug Accountability Form. These forms must be available for inspection at any time.

### **6.3 Measures to Minimise Bias: Randomisation and Blinding**

No blinding will be used in this study.

The study will randomise participants on an ongoing basis to receive either one of the active candidate treatment arms as an add-on to SoC or to receive SoC alone. Randomisation will be stratified by study centre and baseline severity grade.

If additional arms (candidate treatments) are added to or dropped from the study, randomisation will proceed with an equal probability of assignment to each of the remaining arms, except for situations where a patient does not meet the inclusion/criteria for, and hence would be excluded from, one or more of the sub-protocols.

### **6.4 Study Treatment Compliance**

For each candidate agent, the prescribed dosage, timing, and mode of administration may not be changed, except as defined in Section 6.6. Any departures from the intended regimen must be recorded in the electronic case report forms (eCRFs).

Each dose of candidate agent will be administered by a member of the clinical research team that is qualified and licensed to administer the study product. Administration and date, time, and route will be entered into the eCRF.

### **6.5 Concomitant Therapy**

Any medication or vaccine (including over-the-counter or prescription medicines, vitamins, and/or herbal supplements) that the patient is receiving at the time of enrolment (including screening) or receives during the study must be recorded in the eCRF along with:

- Reason for use
- Dates of administration including start and end dates
- Dosage information including dose and frequency

The Medical Monitor should be contacted if there are any questions regarding concomitant or prior therapy.

A list of excluded medications/therapy will be provided for each candidate agent in the corresponding sub-protocol.

### **6.5.1 Rescue Medicine**

Any permitted rescue medications appropriate for the candidate agent administered will be detailed in the corresponding sub-protocol.

## **6.6 Dose Modification**

An Independent Data and Safety Monitoring Committee (IDMC) will actively monitor interim data throughout the duration of the study to make recommendations about early study closure or changes to the study treatment arms.

Details of permitted dose modifications for specific candidate agents will be detailed in the corresponding sub-protocol.

## **6.7 Treatment after the End of the Study**

This is a study in an acute severe respiratory disease and study treatment will not be continued/required following hospital discharge.

## **7.0 DISCONTINUATION OF STUDY TREATMENT AND PATIENT DISCONTINUATION/WITHDRAWAL**

### **7.1 Discontinuation of Study Treatment**

A patient in this study may discontinue their assigned candidate agent for any of the following reasons:

- Patient requests to discontinue study drug.
- Occurrence of any medical condition or circumstance that does not allow the patient to adhere to the requirements of the protocol or patient fails to comply with protocol requirements or study-related procedures.
- Any SAE, clinically significant AE, severe laboratory abnormality (including abnormal liver function test results), intercurrent illness, or other medical condition that indicates to the Investigator that continued participation is not in the best interest of the patient.
- Pregnancy recognised post start and prior to end of study treatment.

Unless the patient withdraws consent, those who discontinue study drug early should remain in the study for further acquisition of endpoint measurements. The reason for patient discontinuation of study drug should be documented in the eCRF.

### **7.2 Patient Discontinuation/Withdrawal from the Study**

- A patient may withdraw from study treatment or the study at any time at his/her own request, or may be withdrawn from study treatment or the study at any time at the discretion of the Investigator for safety, behavioural, compliance, or administrative reasons.
- If the patient withdraws consent for disclosure of future information, the Sponsor may retain and continue to use any data collected before such a withdrawal of consent.
- If a patient withdraws from the study, he/she may request destruction of any residual remaining samples taken and not tested, and the Investigator must document this in the study centre study records. However, any laboratory or test data generated from samples that have already been processed and included in secondary translational research may not be recalled.
- See Schedule of Activities (SoA, Section 1.3) for data to be collected at the time of study discontinuation and follow-up and for any further evaluations that need to be completed.

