| Blood (EDTA) host genome (host DNA) j                           |                 | X        |                                                  |                               |                               |                                           |                                              |
| Mid-turbinate nasal swab viral genome j                         |                 | X        |                                                  |                               |                               |                                           |                                              |

EDTA=ethylenediaminetetraacetic acid; FiO2=fraction of inspired oxygen; PBMC=peripheral blood mononuclear cell; PCR=polymerase chain reaction;

PO2=partial pressure of oxygen; RT PCR=reverse transcription polymerase chain reaction; SARS-CoV-2= severe acute respiratory syndrome coronavirus 2;

SoC=standard of care; SpO2=oxygen saturation; SST=serum separator tube.

Note: Additional assessments, if required, will be defined in the sub-protocol.

a These visits will be performed even if a patient has already been discharged. If discharged prior to scheduled visit, in-person visits are preferred, but recognising that quarantine and other factors may limit the patient's ability to return to the clinic, these visits may be conducted by telephone or with a home visit by study staff. For visits conducted by telephone, it will not be possible to perform some scheduled assessments (eg, vital signs). The Day 29 assessments will also be performed, where possible, for patients who discontinue the study prematurely.

b Medical history includes estimated date and time of first symptoms and number of co-morbidities (eg, respiratory, cardiovascular, metabolic, malignancy, endocrine, gastrointestinal, immunologic, renal).

c Baseline assessments should be performed prior to study drug administration.

d Includes ordinal score, National Early Warning Score 2 (NEWS2), oxygen requirement, noninvasive or invasive ventilator requirement, including start and stop of low- or high-flow oxygen supply or of any form of ventilation etc.

e If done as part of SoC, blood gases results to be fully recorded with date and time.

f For parameters, see [Table 5](#).

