| Primary     | 
Stage 1:
 
Time to 2-point improvement on the 9-point ordinal scale, live discharge, or fit for discharge (as analysed at Day 29), whichever comes first, will be compared with each treatment arm with standard of care (SoC) using log-rank test at the one-sided 0.1 alpha level. Patients in the Stage 1 Intention to Treat (ITT) set will be used.
 
Stage 2:
 
The time to 2-point improvement on the 9-point ordinal scale, live discharge, or fit for discharge (as analysed at Day 29), whichever comes first, analyses will be conducted between the selected treatments plus SoC and SoC alone. The primary endpoint could be re-determined based on Stage 1 results. Patients in the Stage 2 ITT set will be used for the following analyses:
 
The time to 2-point improvement on 9-point ordinal scale, live discharge, or fit for discharge at Day 29 will be conducted between each selected treatment group and control using the log-rank statistic, stratifying for study centre and baseline severity grade, and the p-value associated with the log-rank statistic will be compared at the 2-sided 0.05 alpha level. The hazard ratio between treatment arm and SoC will be estimated using Cox regression, including treatment, age category (age <70 years vs ≥70 years), baseline severity, age category and treatment interaction, baseline severity and treatment interaction as fixed effect, and study centre as random effect.
 |

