#### **9.5.4 Missing Data**

All patients recruited into the study will be accounted for, including those who did not complete the study along with the reasons for withdrawal. Patients who withdraw from the study will have the reasons of withdrawal collected in the eCRF. Non-completers in the endpoints of the response rate analyses will be treated as non-responders. More details will be described in the SAP before database lock.

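### Sections 7.1 and 7.2 disagree on whether an investigator can end a patient's outcome follow-up, which permits avoidable and possibly arm-dependent loss of primary-endpoint data in an open-label trial

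*Protocol*

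**What the plan says.** Section 7.1 lists reasons for stopping the candidate agent. One is that the "patient fails to comply with protocol requirements or study-related procedures". Another covers adverse events, laboratory abnormalities or an "other medical condition that indicates to the Investigator that continued participation is not in the best interest of the patient". It then sets the retention rule: "Unless the patient withdraws consent, those who discontinue study drug early should remain in the study for further acquisition of endpoint measurements". Withdrawn consent is the only exception it names.

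Section 7.2 says a patient may be "withdrawn from study treatment or the study at any time at the discretion of the Investigator for safety, behavioural, compliance, or administrative reasons". Its last bullet refers to the Schedule of Activities for what is collected at study discontinuation and afterwards. Footnote a of that schedule (Section 1.3) says: "The Day 29 assessments will also be performed, where possible, for patients who discontinue the study prematurely".

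Three other statements bear on the point:
- **Blinding (Section 6.3):** "No blinding will be used in this study".
- **Primary analysis (Table 4):** time to response is compared with standard of care (SoC) in Stage 1 "using log-rank test at the one-sided 0.1 alpha level". Stage 2 uses a stratified log-rank test at two-sided 0.05.
- **Missing data (Section 9.5.4):** "Non-completers in the endpoints of the response rate analyses will be treated as non-responders". Further detail is left to the SAP, and no rule is given for withdrawn patients in the time-to-response analysis.

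**The concern.** The same clinical event can lead to two different outcomes for the data. A patient who tolerates the agent badly at Day 5 stays under observation to Day 29 if the site follows 7.1, and may leave the study altogether if it follows 7.2. The investigator making that choice knows the arm. SoC patients have no candidate agent to tolerate or to take as directed, so withdrawals on agent-related grounds would fall mainly in the agent arm.

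At stake are the daily ordinal scores that date a response, and survival status at Days 15 and 60, where mortality is a secondary endpoint. If those who leave are mostly patients who would not have responded, and they are censored on leaving, the arm they leave looks better than it is. A SAP can set a censoring rule, but it cannot recover scores and survival data that sites stopped collecting.

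**Working it through.** **1. The texts side by side.**

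| Event | Under 7.1 | Under 7.2 |
|---|---|---|
| Safety problem | Agent may stop; follow-up continues | Investigator may end treatment or study participation |
| Non-compliance | Agent may stop; follow-up continues | Investigator may end treatment or study participation |
| Withdrawn consent | Follow-up may end | Follow-up may end |

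No sentence ranks one section above the other. The safety item in 7.1 adds to the ambiguity by speaking of participation rather than treatment.

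**2. The design figures reproduce.** With response by Day 29 of 70% (SoC) and 85.5% (agent), HR = ln(1 − 0.855)/ln(1 − 0.70) = 1.604. Schoenfeld events at 1:1 allocation are 4(z_α + z_β)²/(ln HR)².
- Stage 1: 4(1.282 + 0.842)²/(0.4724)² ≈ 81. The protocol states 81.
- Stage 2: 4(1.960 + 1.282)²/(0.4724)² ≈ 188.3, or 189 rounded up. The protocol states 188.

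No stated sample-size figure is wrong because of this point. The protocol gives no dropout allowance; the margin from 54 to 60 per arm is attributed to recruitment uncertainty.

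**3. What early loss could do.** From the protocol: 54 to 60 per arm at one-sided 0.10, and 126 per arm at one-sided 0.025. Assumed, because the protocol gives none: the withdrawal rates, the withdrawal days, censoring at withdrawal, and that only patients who would not respond by Day 29 are removed. Response times are exponential over 28 days with 70% responding in both arms (no true effect), a daily rate of −ln(0.30)/28 = 0.043. Thirty percent of an arm are then non-responders, so removing 5% of an arm removes one sixth of them (3 of 60 patients in Stage 1, about 6 of 126 in Stage 2). Removing 10% removes one third of them.

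Simulated log-rank rejection rates under the null, with at least 4,000 trials per setting where the run size is recorded. Ranges span separate runs.

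| Setting | Stage 1 (nominal 0.10) | Stage 2 (nominal 0.025) |
|---|---|---|
| None removed, or all kept at risk to Day 29 as in 7.1 | 0.10 to 0.11 | 0.023 to 0.028 |
| 5% of agent arm only, censored at Day 5 | 0.17 to 0.19 | 0.08 to 0.09 |
| About 6% of agent arm only, censored Days 3–10 | 0.18 | 0.08 |
| 10% of agent arm only | 0.27 to 0.31 | 0.16 to 0.20 |
| 5% of agent arm, 2.5% of SoC | 0.15 | 0.06 |
| 5% of agent arm only, Day 29 non-response recovered for 80% of them | 0.11 to 0.13 | about 0.03 |
| Equal removal in both arms (about 6% or 15%) | 0.10 | 0.023 to 0.026 |

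The Monte Carlo standard error near 0.18 is √(0.18 × 0.82/4000) = 0.006, so the small differences between runs carry no meaning. The apparent null HR is about 1.07 to 1.08 at 5% and 1.17 at 10%.

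**4. The opposite direction.** Under the design alternative, removing 20% of SoC non-responders (0.20 × 30% = 6% of that arm) cuts power from 0.82 to 0.70 in Stage 1 and from 0.91 to 0.79 in Stage 2.

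**5. What footnote a covers.** The Day 29 visit includes survival status and the ordinal score, so a withdrawn patient can still be shown to be alive or dead, and a non-responder, at Day 29. It does not date a response that happened in between, and its extension to patients who leave the study names Day 29 only, not Day 15 or Day 60.

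**The case against.** The two sections can be read as default and exception. Section 7.1 governs stopping the agent and says patients should remain; 7.2 governs leaving the study. Consent is not the only exit elsewhere either, since 7.3 treats unreachable patients as withdrawn. That reading is possible, but no text states it, and on safety and compliance it leaves the exception as wide as the rule. The drafting conflict stands.

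The stronger objections concern the harm, and most of them hold. A reader might infer that the protocol censors patients at withdrawal and that its type I error is therefore inflated. The documents do not say so: no censoring rule is stated for the primary analysis, and Sections 9.5 and 9.5.4 leave the handling of missing data to the SAP. A reader might also infer that Day 29 mortality loses these patients. Footnote a, reached through 7.2 itself, keeps that assessment where possible, so the inference is too strong.

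Nor does the protocol fix a direction. Behavioural, administrative and procedure-related grounds apply to SoC patients too, and removal from that arm biases the other way. Finally, Section 9.6 bases progression to Stage 2 on the totality of data, so a raised Stage 1 rejection rate does not by itself mean that an inactive agent advances.

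**Conclusion.** The point holds as a conflict between 7.1 and 7.2 that permits avoidable, possibly arm-dependent loss of daily ordinal scores and of survival data beyond Day 29 in an unblinded trial. Footnote a softens it but does not close it, because it applies only where possible, fixes status at one day, and leaves out Days 15 and 60.

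The size is conditional. Rejection under the null of about 0.17 to 0.19 in Stage 1 and 0.08 to 0.09 in Stage 2 requires four assumptions: 5% of the agent arm is removed, none of the SoC arm is, all those removed are non-responders, and all are censored at Day 5. That is a worst case at an assumed rate, not an estimate of what the trial will do. Recovering Day 29 status for most of these patients brings rejection to about 0.11 to 0.13 and 0.03, and equal removal leaves it nominal. The sample-size figures are unaffected. The point merits a short amendment because data not collected cannot be restored at the analysis stage.

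**What to change.** Reconcile 7.2 with 7.1 by separating three things: stopping treatment, stopping study procedures, and ending outcome follow-up. Let investigator discretion in 7.2 cover study treatment and study procedures, and state that it does not end outcome follow-up. Unless consent for data collection is withdrawn, or the patient is lost to follow-up under 7.3, continue to collect the ordinal score and discharge date to Day 29 and survival status at the scheduled contacts. Cross-refer to footnote a, and extend it so that it no longer names Day 29 alone.

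The cost is a short protocol amendment and continued data collection for a few patients, at contacts already in the schedule. The rules for stopping treatment are unchanged.

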### **7.3 Lost to Follow-up**

A patient will be considered lost to follow-up if he or she repeatedly fails to return for scheduled visits and is unable to be contacted by the study centre.

The following actions must be taken if a patient fails to return to the study centre for a required study visit:

- All efforts should be made to ascertain the vital status of the patient.

- The study centre must attempt to contact the patient and reschedule the missed visit as soon as possible and counsel the patient on the importance of maintaining the assigned visit schedule and ascertain whether or not the patient wishes to and/or should continue in the study.
- Before a patient is deemed lost to follow-up, the Investigator or designee must make every effort to regain contact with the patient (where possible, 3 telephone calls and, if necessary, a certified letter to the patient's last known mailing address or local equivalent methods). These contact attempts should be documented in the patient's medical record.
- Should the patient continue to be unreachable, he/she will be considered to have withdrawn from the study.

